### Intervention conditions

The intervention was conducted on a one-on-one basis, was designed to last 45–60 min, and was completed in the same appointment and by the same therapist as the in-person assessment. After the T1 assessment was completed, participants were randomized into their treatment condition and the therapist used the appropriate intervention manual and materials related to the selected condition. At the start of each intervention session, participants are asked to briefly describe the factors they believed to be associated with their suicidal ideation and any patterns they had noticed in the occurrence of the ideation. At the end of each session, participants were provided a list of mental health resources.

### DBT-BSI

The DBT-BSI involved presenting participants with five pre-selected DBT skills [5, 22]:Mindfulness (what to do with one’s attention/mind and how to engage in mindfulness practices);Mindfulness of current emotions (observing and describing emotional experiences; labeling emotions; observing physical sensations over time);Opposite-to-emotion action (blocking the behaviors prompted by emotions and instead acting opposite to or inconsistently with emotional urges);Distraction (distracting attention by thinking about or doing something else); andChanging your body chemistry (applying ice water to the face, engaging in intense exercise, pacing one’s breathing, and progressive muscle relaxation).

### RT

The RT procedures were designed to control for non-specific factors, such as the amount of time spent with a caring assessor, providing a rationale for usefulness of the information presented, and participant expectancies. The intervention was also based on principles of supportive therapy in which the assessor functions as a supportive, validating, and caring individual [23]. The intervention began with an open-ended discussion of the participant’s current life stressors and the ways they attempt to manage stress. Next, a rationale for relaxation was provided which emphasized the importance of building up resources to deal with stressors and difficult events more easily. Relaxation was not introduced as a skill. Instead, the therapist moved into encouraging the participant to try a relaxation practice and then walked the participant through a sensory awareness relaxation activity. The sensory awareness activity was based on a similar practice first developed by Goldfried and Davison [24] and involves the therapist reading a series of questions designed to prompt the participant to notice or pay attention to different sensations. Examples of the types of questions included in the practice are: “Can you feel your hair touching your head?” “Can you imagine something far away?” “Can you notice how one arm is warmer than the other?” The relaxation practice lasted approximately 10–15 min and was followed by a discussion of the impact of the practice on current stress and distress levels.

This type of activity provides confidence in the safety and potential effectiveness of the control condition; namely, there is reason to believe that relaxation techniques may partially serve a distress tolerance function and therefore was likely to provide immediate reduction in distress levels [25, 26]. However, if deficits in emotion regulation and distress tolerance skills are responsible for increased suicidal ideation (as would be predicted by Linehan’s theory [5, 27]), one would expect a greater reduction in suicidal ideation in the DBT-BSI condition over the RT control condition. Talking about skills, presenting relaxation practice as a skill, and problem-solving were all prohibited in the RT control.

### Follow-up

Participants were contacted by phone to schedule and complete their follow-up interviews (T2-T4). At the time of each interview, the next assessment was scheduled and then reminder calls were placed to confirm the appointment and reschedule as needed. Multiple attempts were made to reach each participant for each follow-up assessment to promote retention and to complete follow-up data collection. The follow-up interviews were conducted by research assistants under the supervision of the principal investigator (EW). All research assistants conducting follow-up interviews were kept blind to participants’ assigned intervention condition.

### Power calculation

A power analysis was conducted prior to the start of the study to provide a guide to sample size requirements. Calculations were based on feasible differences in treatment effect at the three-month follow-up assessment (T4). Based on Cohen’s [28] discussion of effect sizes, the effect size from the pilot study was consulted [13]. The effect size for the decrease in suicidal ideation observed during the pilot study was 0.56, which is considered a medium effect. In order to power the study with a medium effect size for detecting changes in suicidal ideation, the study will require 53 participants per intervention condition, using an independent sample *t*-test between the active and control condition (G*Power) [29].

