### Randomization

A computerized minimization randomization algorithm was used to match participants on three variables that may confound analytic results. These three variables are identified gender, history of suicide attempts, and whether the participant was interested in mental health treatment. Participants were randomized using a 1:1 ratio, such that equal numbers of participants were assigned to each condition. Following completion of the T1 assessment, the therapist entered the participants’ data related to the three potentially confounding variables into the computerized program and participants were randomly allocated to one of the two conditions.

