**Fig. 1 Fig1:**
[figure not shown]
CONSORT Diagram

The total intent-to-treat sample size was 13 participants fewer than the pre-trial power analyses indicated would be necessary to detect a medium effect size change in suicidal ideation; however, based on power calculations for the full sample, this reduced sample will provide 80 % power to detect differences between the two groups in the medium range (Cohen’s d between 0.5 and 0.6 [28]) and less than adequate power to detect small differences. Additionally, the relatively high rate of retention will still allow us to draw meaningful conclusions from the primary and secondary outcomes of interest.

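### As worded, the sample size uses a pilot decrease in suicidal ideation, with no comparator given, as the DBT-BSI versus RT difference at 12 weeks

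*Protocol article*

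**What the plan says.** The Power calculation section of the protocol article sets its target as a treatment difference at T4, the three-month follow-up. The only effect it reports comes from the pilot study: "The effect size for the decrease in suicidal ideation observed during the pilot study was 0.56, which is considered a medium effect". It names no pilot comparator, no time point and no standard deviation by which the change was divided. It then concludes that "the study will require 53 participants per intervention condition, using an independent sample" t-test of the active against the control condition.

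The RT section describes the control as based on supportive therapy and as potentially effective. It says that "relaxation techniques may partially serve a distress tolerance function and therefore was likely to provide immediate reduction in distress levels". The same section predicts a larger fall in suicidal ideation under DBT-BSI than under RT, so the trial's contrast is a difference between two decreases.

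After the CONSORT figure, the article notes that the sample fell 13 short of this calculation. It adds that "this reduced sample will provide 80 % power to detect differences between the two groups in the medium range", giving Cohen's d of 0.5 to 0.6 as that range.

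**The concern.** A decrease observed during a study is, on its plain reading, a change within participants. An independent-samples t-test needs something else: the difference between two arms at one time point, divided by the between-person SD. If both quantities use the same SD, they agree only when the control arm does not change.

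That is hard to assume here. Everyone enters with suicidal ideation in the past week, so some fall in both arms through regression to the mean is plausible. Both arms also get time with a supportive therapist and a list of mental health resources.

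At stake is the stated basis for 53 per arm and for describing the trial as powered for a medium effect. The article uses that calculation as the benchmark for its shortfall. A reader who accepts it may give a non-significant contrast more weight than the sample can bear.

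**Working it through.** **Inputs.** From the Power calculation section: effect 0.56, 53 per condition, independent-samples t-test, time point T4. From the Randomization section: "Participants were randomized using a 1:1 ratio, such that equal numbers of participants were assigned to each condition". From the Status of the trial section: 93 attended the in-person appointment and 70 were retained to 12 weeks (23/93 = 24.7% lost). Assumed: two-sided alpha 0.05 and 80% power for the pre-trial calculation (80% is stated only for the achieved sample), 47/46 for the 93, and 35 per arm for the 70.

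**1. Reproduce the stated figure.** The normal approximation is n per arm = 2(1.960 + 0.842)²/d² = 15.70/d².
- d = 0.56: 15.70/0.3136 = 50.1, so 51. The exact noncentral t gives 52.
- d = 0.55: exact t gives 53.
- d = 0.50, the conventional medium value: exact t gives 64.

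Under these settings, 53 is reproduced only with a between-arm d of about 0.55 to 0.56. Other settings fit less well: d = 0.56 one-sided needs 41 (80% power) or 56 (90%), and two-sided at 90% it needs 68. One-sided at 80% power, d = 0.50 gives 51, which is near 53 but not equal to it. The arithmetic is therefore sound, and 0.56 is the only effect in the text that leads to it.

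**2. What the test needs.** On a common SD, d = (decrease in DBT-BSI − decrease in RT)/SD. If DBT-BSI repeats 0.56 and RT achieves a fraction f of it, then d = 0.56(1 − f).

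**3. Illustration.** The article gives no value for f, so the values below are assumptions. Exact power uses noncentrality d√(n₁n₂/(n₁+n₂)) on n₁+n₂−2 degrees of freedom.

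| f | d | n per arm for 80% | Power, 53 per arm | Power, 47/46 | Power, 35/35 |
|---|---|---|---|---|---|
| 0 | 0.56 | 52 | 81% | 76% | 64% |
| 0.25 | 0.42 | 90 | 57% | 52% | 41% |
| 0.50 | 0.28 | 202 | 30% | 27% | 21% |

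**4. Dependence on the standardiser.** If 0.56 was divided by the SD of the change scores, the value on the raw SD is 0.56√(2(1 − r)), where r is the pre-post correlation.
- r = 0.7: 0.56 × 0.775 = 0.43, even with no change in RT.
- r = 0.5: 0.56 × 1 = 0.56.
- r = 0.3: 0.56 × 1.183 = 0.66 with no change in RT, and 0.66 × 0.75 = 0.50 if RT achieves a quarter.

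So the direction of the error is fixed only when the standardiser is known.

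**5. What the trial can detect.** The d with 80% power in a two-sided 5% t-test depends on n alone: 0.55 with 53 per arm, 0.59 with 47/46 and 0.68 with 35/35. The approximate 95% CI half-widths are 1.99√(1/47 + 1/46) = 0.41 SD with 93 and 2.00√(2/35) = 0.48 SD with 70.

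**The case against.** The strongest reply is that the pilot's design is not shown. An article may leave such detail to the study it cites, and 0.56 could be a controlled difference in decrease. The article's wording is loose elsewhere too: it speaks of detecting changes in ideation when it means a t-test between conditions. This stands. A reader might infer that 53 certainly rests on an uncontrolled pre-post effect, but the document does not establish that.

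Three other inferences also go too far:
- **The between-condition effect must be below 0.56.** This holds only on a common standardiser (step 4).
- **The pilot value overstates what the trial can detect.** The detectable d is set by n, alpha and power. What may be overstated is the expected contrast.
- **A null result is likely.** That depends on the assumed RT response. With 93 participants and f = 0.25, power is about one half.

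It is also fair to say that the RT section speaks of immediate distress, not of ideation at 12 weeks. The planned analysis is a hierarchical model over repeated measures, so t-test power is only a guide to it. Finally, the paragraph after the CONSORT figure already gives a between-group range for the full sample, and 0.59 lies inside it.

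These replies limit the claim but do not remove it. The text gives a decrease as the input and a between-arm test as its use, and nothing connects the two. The later range of 0.5 to 0.6 applies to all 93, whereas the calculation was made for T4, where 70 were observed.

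**Conclusion.** The point holds conditionally. As worded, a pilot decrease of 0.56 with no comparator or standardiser was used as the between-condition d at T4. If it is a pre-post change, it is not the expected DBT-BSI versus RT contrast. On a common standardiser, it then overstates that contrast by whatever improvement RT participants show.

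The size of that overstatement cannot be obtained from the document. The range of 57% down to 30% power at 53 per arm is an illustration that assumes RT achieves a quarter to a half of the decrease. One figure does not depend on what 0.56 means: with 35 per arm at T4, a simple t-test has 64% power at d = 0.56 and reaches 80% only at about 0.68.

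Severity is moderate. Enrolment is complete, so the sample size cannot change, but analysis was still under way when the article was written and the interpretation could still be set correctly.

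**What to change.** In the Power calculation section, state what 0.56 is: within-group or controlled, against which comparator, at what time point and divided by which SD. If it was a controlled between-group effect, say so and name the comparator. If it is within-group, remove it as the justification for between-condition power.

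In either case, state the between-condition d detectable with 80% power by a two-sided 5% t-test: about 0.59 with all 93 participants and about 0.68 with the 70 observed at T4. Give the assumed arm sizes, and note that power under the planned hierarchical model may differ.

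Report the DBT-BSI versus RT contrast with a 95% CI, which matches the aim of estimation stated at the start of Methods/Design. Say that a non-significant result is not to be read as no effect.

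The change is to wording only. The cost is a less favourable power statement.

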### Analyses

Hierarchicial linear modeling [30, 31] will be used to assess differences between conditions over time. The within-subjects model (level-1), will include the estimates of the individual changes in repeated measures of suicide ideation, emotion dysregulation, skills use, depression, and anxiety assessed over time. The between-subjects model (level-2), will incorporate condition assignment as a predictor of the Level-1 growth parameters. Effect sizes will be computed using Feingold’s formula [32] and interpreted using Cohen’s guidelines [28].

Intervention effects for binary outcomes (i.e., use of the skills taught during the intervention, mental health treatment contact, and suicidal behaviors) will be evaluated in much the same way as continuous outcomes. Specifically, an extension of the generalized linear model, the generalized estimating equation (GEE) approach will be used [33, 34]. GEE is an increasingly popular approach to longitudinal and repeated measures designs, especially in the case of binary and categorical outcomes [35] owing to its simplicity relative to mixed models for fitting binary data. Effect sizes will be computed using relative risk ratios [36].

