## Methods/Design

In addition to evaluating the safety and feasibility of delivering this intervention to suicidal individuals who are not otherwise engaged in mental health treatment, this RCT’s aim is to estimate the immediate (one-week) and long-term (four- and 12-week) degree of change and variability of response to the DBT-BSI relative to a relaxation training (RT) control on the primary outcomes of suicidal ideation, emotion dysregulation, and skills use. Secondary outcomes of depression, anxiety, self-efficacy, and treatment utilization are also examined. Specifically, we hypothesize that, relative to the RT control condition:DBT-BSI will result in lower levels of suicidal ideation and emotion regulation;DBT-BSI will result in higher levels of skills use, in general, and in greater use of the specific skills taught in the DBT-BSI;DBT-BSI will result in lower levels of depression and anxiety; andDBT-BSI will result in greater utilization of mental health resources during the follow-up period.

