### Procedure

Interested individuals who contacted the research office underwent an initial phone screening interview (T0) to determine study eligibility. Those who were eligible for the study were scheduled for on-site baseline assessment (T1) and intervention procedures. Following this in-person assessment and intervention appointment, participants completed three telephone follow-up interviews at 1- (T2), 4- (T3), and 12- (T4) weeks. Assessment domains include cognitive impairment (6-Item Cognitive Impairment Test) [14], suicidal ideation (Scale for Suicidal Ideation) [15] and suicidal behaviors (Lifetime Parasuicide Count) [16], emotion dysregulation (Difficulties in Emotion Regulation Scale) [17], depression (Patient Health Questionnaire Depression Module) [18], anxiety (Beck Anxiety Inventory) [19], skills use (DBT Ways of Coping Checklist) [20], and treatment utilization (Treatment History Interview; Linehan & Heard, unpublished work). Additionally, measures to prompt assessment and documentation of suicide risk were included (University of Washington Risk Assessment Protocol and the University of Washington Risk Assessment and Management Protocol) [21]. Participants were eligible to receive up to $45 in compensation for completing all study assessments (T1 = $5, T2 = $10, T3 = $10, T4 = $20).

The phone screening interview (T0) was conducted by the principal investigator and research assistants under the supervision of the principal investigator. The on-site baseline assessment (T1) and intervention appointments were conducted by three master’s-level graduate students in doctoral psychology programs. Weekly supervision and consultation were utilized for ongoing training and to monitor adherence to the intervention procedures.

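### For the continuous outcomes, condition is tied only to growth parameters of unstated form; with a single slope, that coefficient does not estimate the week-1, week-4 and week-12 effects the trial aims at

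*Protocol article*

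**What the plan says.** - **Aim (Methods/Design).** The trial is to "estimate the immediate (one-week) and long-term (four- and 12-week) degree of change and variability of response" to DBT-BSI relative to relaxation training. The primary outcomes are suicidal ideation, emotion dysregulation and skills use.
- **Exposure and timing (Intervention conditions, Procedure).** There is one session, which "was completed in the same appointment and by the same therapist as the in-person assessment". On order, the text says: "After the T1 assessment was completed, participants were randomized into their treatment condition". Afterwards "participants completed three telephone follow-up interviews at 1- (T2), 4- (T3), and 12- (T4) weeks".
- **Sample size (Power calculation).** The target is 53 per arm for an effect of 0.56, using an independent-samples t-test on the difference at T4.
- **Analysis (Analyses).** Continuous outcomes go to a two-level hierarchical linear model. Level 1 describes each person's change over time, and level 2 "will incorporate condition assignment as a predictor of the Level-1 growth parameters". The section states no growth form, time coding, centring or contrast at a named visit. Binary outcomes, including use of the taught skills, go to generalized estimating equations and are outside this point.

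**The concern.** The aim and the sample size concern differences between arms at named visits. The only condition effect described for the continuous outcomes is on the parameters of a trajectory. These agree when the trajectory has the right shape.

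Here the shape is in doubt. The intervention is a single session at week 0, so its effect may well appear between T1 and T2 and then hold or fade. Visits at weeks 0, 1, 4 and 12 give the last visit most of the leverage on a straight line, so the slope largely reflects what happens between weeks 4 and 12. T1 also precedes randomisation, so the expected arm difference there is zero. A model that lets condition predict the intercept can book part of a real early effect as a baseline difference.

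At stake is whether an early benefit on a primary outcome is reported, nearly lost, or described by a coefficient pointing the other way.

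**Working it through.** **1. The plan's own figure.** A two-sample t-test with d=0.56, two-sided alpha 0.05 and 80% power (alpha and sidedness are not stated, so assumed) needs 52 per arm; d=0.55 gives 53. The stated 53 is reproduced. With 93 participants split 47/46, 80% power is reached at d=0.587, inside the stated range of 0.5 to 0.6. The sizing is sound for a T4 difference, which is not the quantity the Analyses section describes.

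**2. Inputs.** From the article: visit times 0, 1, 4, 12; d=0.56; N=93. Assumed: SD 1, a 47/46 split, complete data, compound symmetry with correlation ρ from 0.4 to 0.7, and growth linear in weeks with free intercepts. Positive values favour DBT-BSI.

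**3. Slope.** In this setting generalised least squares equals ordinary least squares. Mean time is 4.25; the deviations are -4.25, -3.25, -0.25 and 7.75; their squares sum to 88.75. With d_t the true arm difference at week t, b = Σ(t - 4.25)d_t / 88.75, the implied 12-week change is 12b, and the fitted baseline difference is a = mean(d_t) - 4.25b.

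- Sustained step (0, 0.56, 0.56, 0.56): b = 2.38/88.75 = 0.0268; 12b = 0.32; a = 0.42 - 0.114 = 0.31.
- Halves by week 12 (0, 0.56, 0.42, 0.28): b = 0.245/88.75 = 0.0028; 12b = 0.03; a = 0.30.
- Fades to zero (0, 0.56, 0.28, 0): b = -1.89/88.75 = -0.0213; 12b = -0.26; a = 0.30.
- True linear build-up to 0.56: 12b = 0.56; a = 0.

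**4. Power of the slope test.** SE(b) = √[(1-ρ)(1/47+1/46)/88.75], which is 0.01705 at ρ=0.4 and 0.01206 at ρ=0.7. Power is Φ(|b|/SE - 1.96), plus the far tail where it matters.

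- Sustained: z = 1.57 to 2.22, power 35-60%.
- Halves: z = 0.16 to 0.23, about 5%.
- Fades to zero: z = -1.25 to -1.77, significant in the wrong direction in 24-42% of trials.

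**5. Baseline-adjusted contrast at one visit.** SE = √[(1-ρ²)(1/47+1/46)], which is 0.190 at ρ=0.4 and 0.148 at ρ=0.7. A 0.56 difference gives z = 2.95 to 3.78, power 84-97%. That applies at week 1 in the three early-effect patterns, and at week 12 under the sustained step or linear build-up.

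**6. Fitted arm differences, a + bt.**

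| True pattern | Week 1 (true 0.56) | Week 4 | Week 12 |
|---|---|---|---|
| Sustained | 0.33 | 0.41 | 0.63 |
| Halves | 0.31 | 0.31 | 0.34 |
| Fades to zero | 0.28 | 0.22 | 0.05 |

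Every sign is right, but week 1 is about half to three-fifths of the truth.

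**7. Other forms.** With free intercepts, the fading pattern also gives a reversed slope under wave-number coding (-0.028 per wave) and log(week+1) coding (-0.049 per log unit), but more weakly. With a common intercept the slope is adverse or near zero in all three codings. For the sustained step at ρ=0.7, slope power rises to 91% (wave number) and 87% (log), so that loss is mainly a feature of linear weeks. A piecewise form with a knot at week 1 recovers 0.56, 0.53 and 0.50 at week 1 for the three early-effect patterns.

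**8. Dropout.** Only the final 70/93 (75%) is documented. Assuming retention of 90%, 83% and 75% and ρ from 0.4 to 0.6, simulation gives 30-42% slope power for the sustained step against 71-83% for a baseline-constrained week-12 contrast. The wrong-direction rate for the fading pattern is 16-24%.

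**The case against.** The strongest reply is that the article never says the growth is linear. A piecewise model also has growth parameters and would recover the week-1 effect. An intercept is a growth parameter too: with time centred at week 12, the condition effect on the intercept is the T4 difference. A full analysis plan, not shown, may settle all of this. This stands. A reader might infer that growth parameters cannot estimate the stated effects at all; the text does not support that, and the point holds only for a single-slope form.

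Second, the slope is one of two parameters. For the sustained step, the fitted week-12 difference has about 87% power, although it overshoots (0.63 against 0.56). A reader might infer that a fading benefit would be reported as harm. That does not follow: only the slope reverses, while the fitted visit differences stay favourable. What remains is the shrunken week 1 and the missing statement of which quantity is to be reported.

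Third, sizing with a simple t-test and analysing longitudinally is common and no contradiction in itself. The aim also covers variability of response, which individual growth models describe well and a visit-factor model does not. Both are fair, and are reasons to keep the growth model in support.

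Fourth, one might infer bias from T1 being done in person by the therapist and T2-T4 by telephone. The change of mode applies to both arms and largely cancels from their comparison, so it adds little.

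Finally, the calculations use compound symmetry without individual slopes, and the fading shapes are hypothetical.

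**Conclusion.** The point holds in a conditional form and is worth acting on. For the continuous outcomes, the article names week-1, week-4 and week-12 differences as its aim and T4 as its sizing basis, but states a condition effect only on growth parameters of open form. If a single slope linear in weeks is used, the condition-by-time coefficient understates a sustained 0.56 SD step (0.32 SD, 35-60% power), nearly misses one that halves (0.03 SD, about 5%) and reverses one that fades to zero (-0.26 SD). Fitted visit differences keep their sign but put week 1 at about 0.3 SD.

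These sizes rest on the assumptions listed in the check; the correlation and the effect shapes are not in the article. The article does not show that the analysis is wrong under every growth form. Nor does the point reach the binary outcomes.

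**What to change.** For the continuous outcomes:

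- Fit the mixed model with time as a four-level factor, and constrain the arms to a common mean at T1 or adjust for the T1 score.
- Report condition contrasts at weeks 1, 4 and 12, and name the T4 suicidal-ideation contrast as the test that matches the power calculation.
- Compute effect sizes from these contrasts.
- Keep the growth model as a supporting analysis that describes variability of response, and state its form and time coding.

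The cost is analysis wording and a few lines of code on data already collected; the article says analysis was still ongoing. The model has a few more parameters and loses some power if the effect truly builds linearly. At ρ 0.5 to 0.7 with complete data, a correctly specified common-intercept slope then has 90-98% power, against 87-96% for the baseline-adjusted week-12 contrast by t-test.
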